### Early termination and stopping rules

As noted, the safety of the trial will be monitored on an ongoing basis throughout the study. The Data Safety Monitoring Board (DSMB) will conduct a formal evaluation of trial progress including considerations of participant risk vs. benefits after the recruitment of 25 participants or sooner if required (for instance, in the event of a serious adverse event). The study may be terminated prematurely by the Coordinating and/or Principal investigator or his/her designee, the DSMB, and the sponsor if:
The number and/or severity of adverse events justify the discontinuation of the study.New data becomes available which raises concern about the safety of the study drug, so that continuation might cause unacceptable risks to participants.Recruitment is slow and it is assessed that the trial is unlikely to finish.

After such a decision, the Investigator or designee will contact all participants promptly, and written notification of study termination will be sent to the Reviewing Ethics Committee and relevant Governance Offices. A study closure advice will also be sent to the Therapeutic Goods Administration on the approved form. The Australian Clinical Trial Registry entry will also be updated accordingly.

### Participant reimbursement and compensation

Participants will be reimbursed for out of pocket expenses, inconvenience and time involved by the provision of prepaid gift cards to an Australian retail outlet. A $20 gift card will be provided at the baseline visit and weeks 2, 4 and 6 (total reimbursement $80). For those participants who consent to the blood test an extra $10 will be provided at the baseline visit and week 6 (total reimbursement $100). If the study is terminated by the Investigator prior to completion, or a participant withdraws or is withdrawn from the study before completion, a pro-rata payment will be made at the discretion of the Investigator. The clinical trial insurance will reimburse participants for costs of medical care that occur as a result of complications directly related to participation in this study.

### Data management and monitoring

A screening log will be utilised to track potential participants and also record the counts of individuals approached, consented, meeting inclusion/exclusion criteria, withdrawals, and completion (in keeping with standard CONSORT diagram requirements). The case report form (CRF) will comprise of the hard copy questionnaires, clinical assessments and measures. These de-identified data will be retained in a secure room, in a locked filing cabinet, at each site. De-identified data from the CRFs will be entered into REDCap, which is a secure (encrypted to health service standard, housed on a server behind the University of Queensland firewall), web-based application for building and managing online surveys and databases. Delegated research assistants will be trained in, and responsible for, entering data into the database. Upon completion and resolution of monitoring and data management queries, the clinical trial database will be closed. A copy of the PICF will be stored in a secure room in a locked filing cabinet separate from the CRFs.

The Investigator, Project Manager or their delegate at each site will organise the retention of documentation relating to the study (source documents, informed consent forms, approvals) for a period of at least 15 years or the maximum time frame as determined by local regulations, whichever is the longest.

### Statistical analysis

We will compare demographic and clinical differences between the groups at baseline (Fisher exact test for nominal variables and Mann-Whitney test or independent sample t test for continuous variables). All data will be analysed, regardless of whether participants withdrew spontaneously or were withdrawn by the investigator. Efficacy will be assessed according to standard Intention to Treat (ITT) analytic procedures (i.e. for those who do not complete the 6-week study period, we will carry forward their last observation on the study outcomes). A secondary analysis will also be conducted including participants who (1) were in the trial for all 6 weeks, (2) were treatment adherent ≥80% and (3) had no other major protocol violations. Missing values will be addressed using a mixed-effects model repeated measures analysis which is robust in maintaining statistical properties of tests. Mean changes in clinical assessment will be assessed using mixed-model repeated-measure (MMRM) methods with treatment, week, and treatment-week interaction as fixed effects and intercept as the only random effect; baseline value will be the covariant. *P* values will be based on 2-tailed tests with significance levels of 0.05 corrected for multiple comparisons. A more detailed statistical analysis plan will be finalised before database lock.

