### Sample size justification

The primary analysis will be a mixed effect repeated measures analysis comparing total PANSS scores across 4 time points (baseline, 2, 4, and 6 weeks) across 4 dose groups (placebo, 1000 mg, 2000 mg and 4000 mg per day). A recent study by Scott et al. [24, 26] observed a standard deviation for total PANSS score of around 15 for all subjects, and closer to 10 for cases with baseline PANSS scores > 75. The autoregressive (AR(1)) correlation between weeks was estimated at 0.815. Assuming a decrease in PANSS scores similar to this previous study, this study has at least 80% power to detect an effect size of 0.55 between treatments with a sample size of 52 participants, incorporating an allowance for 20% attrition.

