### Clinical outcome measures

The severity of schizophrenia symptoms as measured by the Positive and Negative Syndrome Scale (PANSS) total score will be the primary continuous outcome measure. The mean change in scores from baseline to week 6 (end of the study) will be compared between study arms.

Average change in scores from baseline to week 6 (end of the study) in the following secondary clinical outcome continuous measures will also be included:
PANSS subscale scores, reflecting the severity of positive and negative symptoms and general psychopathology.Global Assessment of Function (GAF), a numeric scale (1 through 100) used by physicians to rate subjectively the social, occupational, and psychological functioning of adults.Clinical Global Impression (CGI) which is used to measure symptom severity, treatment response and the efficacy of treatments in treatment studies of patients with schizophrenia.Patient Global Impression (PGI) is a global index that is used to rate the response of a condition to a therapy (transition scale).

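### Two unreconciled missing-data rules govern the efficacy analysis: carry-forward for non-completers, presented as ITT, and a mixed model; the carry-forward rule can bias the dose contrasts

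*Protocol article*

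**What the plan says.** In the protocol article, the Statistical analysis section states two rules for the same outcomes.

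- Rule A: "Efficacy will be assessed according to standard Intention to Treat (ITT) analytic procedures", explained by an i.e. in brackets: "for those who do not complete the 6-week study period, we will carry forward their last observation on the study outcomes".
- Rule B, two sentences later: "Missing values will be addressed using a mixed-effects model repeated measures analysis which is robust in maintaining statistical properties of tests". The next sentence names the model: "Mean changes in clinical assessment will be assessed using mixed-model repeated-measure (MMRM) methods", with a random intercept and the baseline value as covariate.

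The Sample size justification supports rule B: "The primary analysis will be a mixed effect repeated measures analysis comparing total PANSS scores across 4 time points". It does not mention carry-forward. It sets the sample at 52, "incorporating an allowance for 20% attrition", and assumes that PANSS falls as it did in the earlier early-psychosis trial. The primary contrast is under Clinical outcome measures: "The mean change in scores from baseline to week 6 (end of the study) will be compared between study arms".

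The only analysis labelled secondary in the Statistical analysis section is the one in adherent completers. No text makes LOCF a sensitivity analysis or confines the mixed model to intermittent gaps.

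**The concern.** The two rules give different week-6 results for anyone who leaves early. Under rule A a non-completer's last PANSS stands in for every later visit and enters the model as if measured. Under rule B those visits stay missing, and the model uses the participant's observed visits under a missing-at-random assumption.

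The i.e. is also a conceptual slip. Intention to treat fixes who is analysed and in which arm; it does not prescribe how missing values are filled.

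The stake is the dose comparison. Carry-forward freezes a dropout at an early point of a course that the plan itself expects to move. If dropout differs by arm, that freezing alone can create, hide or enlarge a difference between arms. Differential dropout is conceivable here: Participant withdrawal includes removal for non-adherence and for serious events attributed to study medication, and Dose justification notes that the highest dose has not been used in schizophrenia. With 13 per arm, two or three dropouts can move an arm mean.

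**Working it through.** **The plan's own figure.** If 0.55 is read as Cohen's f in a four-group F test at two-sided 0.05, 41 participants give power 0.81, and 41/(1 − 0.20) = 51.25, rounded up to 52. The stated N therefore reproduces on that reading, although the protocol does not name the index. The missing-data conflict does not change N. The attrition allowance means 0.20 × 52 = 10.4 expected dropouts, or 2.6 per arm.

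**Inputs from the protocol (Sample size justification):** SD 15, weekly AR(1) correlation 0.815, 20% attrition, and a falling PANSS of unstated size. Allocation is 1:1:1:1, so 13 per arm.

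**Assumptions, not in the protocol:** linear change over six weeks; dropouts' last visit at week 0, 2 or 4 with equal probability; a placebo change P of 0, −5 or −10; arm-specific dropout of 10%, 20% or 30%; and a true week-6 difference D of −8.25 (0.55 × 15, here reading 0.55 as a standardised pairwise difference, for illustration only).

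**Formula.** A dropout retains on average (0 + 1/3 + 2/3)/3 = 1/3 of the week-6 change. With dropout proportion p, an arm retains

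R(p) = (1 − p) + p/3 = 1 − 2p/3,

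so R(0.1) = 0.933, R(0.2) = 0.867 and R(0.3) = 0.800. The expected LOCF difference is (P + D) × R(p_active) − P × R(p_placebo).

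| Placebo change P | True difference D | Dropout placebo / active | LOCF difference |
|---|---|---|---|
| any | −8.25 | 20% / 20% | −7.15 |
| 0 | −8.25 | 10% / 30% | −6.60 |
| −5 | −8.25 | 10% / 30% | −5.93 |
| −10 | −8.25 | 10% / 30% | −5.27 |
| −10 | −8.25 | 30% / 10% | −9.03 |
| any | 0 | 20% / 20% | 0 |
| 0 | 0 | 10% / 30% | 0 |
| −5 | 0 | 10% / 30% | +0.67 |
| −10 | 0 | 10% / 30% | +1.33 |
| −10 | 0 | 30% / 10% | −1.33 |

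Two rows in full:

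- Row 1: −8.25 × 0.867 = −7.15, a loss of 1.10/8.25 = 13%.
- Row 4: −18.25 × 0.800 = −14.60 and −10 × 0.933 = −9.33; the difference is −5.27, a loss of 2.98/8.25 = 36%.

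**Timing.** If nobody leaves before week 2 (last visit at week 2 or 4, equally), R(p) = 1 − p/2. Equal 20% dropout then costs 10%. The 10%/30% case gives −18.25 × 0.85 + 10 × 0.95 = −6.01, a loss of 27%.

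**Simulation check** (2,000 replicates, SD 15, weekly AR(1) 0.815, P = −10, D = −8.25, dropout unrelated to the scores):

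| Per arm | Dropout placebo / active | LOCF estimate | Likelihood estimate on observed data |
|---|---|---|---|
| 13 | 20% / 20% | −7.4 | −8.5 |
| 13 | 10% / 30% | −5.1 | −8.1 |
| 100 | 20% / 20% | −7.0 | −8.2 |
| 100 | 10% / 30% | −5.2 | −8.3 |

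At 13 per arm the Monte Carlo standard error is about 6.5/√2000 = 0.15, so the likelihood estimates agree with −8.25 to within about two such errors. Letting dropout depend on observed scores gave similar results at 13 per arm (LOCF −7.5 and −5.1; likelihood −8.4 and −8.4). The likelihood estimator used an unstructured covariance, not the protocol's random intercept, so this check supports analysing observed data rather than that particular covariance choice.

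**The case against.** Four points can fairly be made for the plan.

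- **The rules can coexist.** The carry-forward clause covers only people who do not finish six weeks. A completer who misses week 2 or 4 still has a gap for the model to handle. A reader might infer that LOCF leaves the model no missing values at all; the text does not support that. This reading is nowhere stated, however, and it would still leave LOCF in the main efficacy analysis.
- **The primary model is named.** The Sample size justification names the mixed model, and the Statistical analysis section repeats it. The document leans towards rule B. That makes the carry-forward clause easier to remove, but does not remove it.
- **A choice made after seeing arm results is unlikely.** A reader might infer that two rules leave room to pick the better result. Under Randomisation, allocation concealment and blinding procedure, data analysts are blinded and allocations are withheld until lock, and a detailed analysis plan is due before lock. A late choice would therefore normally be made blind to arm. The published conflict remains, and the later plan must depart from one of the two sentences.
- **The bias is conditional and modest against the noise.** A reader might take the 36% as a property of the trial. It requires an assumed −10 trend and a 10%/30% dropout split (about 1.3 versus 3.9 people per arm). The standard error of a pairwise contrast at 13 per arm is about 5.6 points, so a 1.33-point null bias is about a quarter of one standard error, and simulated null rejection stayed near 5% (5.4%).

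The Background also attributes the improvement in both arms of the early-psychosis trial partly to early, treatment-responsive illness, whereas this trial enrols refractory patients. Yet the Sample size justification assumes a similar decrease, so some downward trend is the plan's own assumption.

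**Conclusion.** The point holds as a conflict in the text, together with a stated rule that would worsen the result if followed. The protocol fixes two rules for the same outcomes and does not rank them, so this is not a detail left open for the analysis plan. It should be resolved before database lock because it concerns the primary efficacy result.

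LOCF can bias the dose contrasts; the documents do not show that it will, or in which direction. Under the stated assumptions, equal 20% dropout attenuates a growing effect by 10% to 13%, depending on dropout timing. A 10%/30% split turns −8.25 into −5.3 to −6.6 as the assumed placebo change goes from −10 to 0, with last visits spread over weeks 0, 2 and 4. With a −10 change the reverse split overstates the effect (−9.03). Under a true null the bias is up to about 1.3 points either way; it halves with a −5 trend and is zero if scores are flat or dropout is equal. Only the SD, the correlation and the 20% overall attrition come from the protocol. The case rests on the unreconciled rules, not on any one of these figures.

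**What to change.** - Delete the carry-forward clause.
- Define ITT as all randomised participants analysed in their assigned arm.
- State that the single primary analysis is the MMRM on all observed post-baseline PANSS totals (weeks 2, 4 and 6), with baseline as covariate, under missing-at-random and without single imputation.
- Participants with no post-baseline visit supply no outcome data to this model, so report their number by arm.
- If LOCF is kept, label it as a sensitivity analysis. Banning it altogether would be a preference, not a necessity.
- A simple missing-not-at-random sensitivity analysis may be added in the analysis plan; with about 10 expected dropouts over four arms it should stay simple.

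The cost is about one sentence of rewording and slightly more analysis work. Sample size, visits and data collection do not change.

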### Study design

The design is a randomised, placebo-controlled, double-blind parallel-group trial to determine the dose of sodium benzoate required for add-on treatment of patients with treatment-refractory schizophrenia. The study is a phase II dose-finding study with secondary endpoints which comprise a pharmacokinetic/pharmacodynamics investigation. This study will include 52 individuals with treatment-refractory schizophrenia. Patients will be given 1000 mg (500 mg bd), 2000 mg (1000 mg bd) or 4000 mg (2000 mg bd) daily of sodium benzoate or placebo. Participants will receive either active treatment (1000, 2000 or 4000 mg/day) or placebo in a 1:1:1:1 ratio. This study medication will be in addition to participants’ routine care, defined as ‘individualized combinations of psychopharmacology, behavioural interventions, rehabilitation and associated clinical services’ in keeping with Queensland Health standards of care. Face-to-face clinical assessments will be at baseline (week 0) and weeks 2, 4 and 6. Weekly phone contact will occur in weeks between face-to-face visits. The SPIRIT reporting guidelines have been used in this study protocol and a spirit checklist has been completed [38].

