### Study population

Fifty-two (52) participants will be recruited through the mental health services at Metro North Hospital and Health Service and West Moreton Hospital and Health Services in Queensland, Australia. Recruitment to the study will be promoted by trial investigators working as clinicians in the study sites. This will ensure staff and consumers at the study sites are well informed about the study.

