### Randomisation, allocation concealment and blinding procedure

Participants will be randomised into one of the treatment groups using a computer-generated randomisation table once written consent has been obtained and the baseline assessments have been completed. Clinicians from participating mental health services will inform potential participants about the study. If interested and agreeing to be contacted, a member of the research team who is independent of the person’s clinical care will communicate further details about the study with the potential participant. If still wishing to participate, consent from participants will be obtained by the researcher. Their capacity to understand the risks and benefits of participation will be assessed on an ongoing basis in compliance with Australian National Health and Medical Research Council guidelines regarding ethical conduct in human research. Participants will receive either active treatment (1000, 2000 or 4000 mg/day) or placebo in a 1:1:1:1 ratio.

The randomisation will be double-blind. An independent biostatistician will generate the randomisation list which will be provided to the manufacturer and to the Princess Alexandra Hospital Pharmacist. All medication will be blinded to the study personnel (including data analysts), research pharmacist and the patient. Sodium benzoate and placebo capsules will be identical in terms of packaging, appearance, colour and taste. Treatment allocations will not be disclosed to the Investigator or any study personnel before the database is locked, unless in an emergency which requires unblinding.

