### Study restrictions

There are no restrictions to participants during the study in terms of concomitant medication, exercise or ambulation.

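### The efficacy model fixed in the article has no health-service term although two services recruit: a small, nearly free loss of precision, not a bias

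*Protocol article*

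**What the plan says.** All references are to the protocol article.

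- **Study population:** the 52 participants are "recruited through the mental health services at Metro North Hospital and Health Service and West Moreton Hospital and Health Services in Queensland, Australia".
- **Study design and Study restrictions:** study medication is added to routine care, described as "individualized combinations of psychopharmacology, behavioural interventions, rehabilitation and associated clinical services". The same sentence ties that care to the standards of the state health department. On other treatment, the article says "There are no restrictions to participants during the study in terms of concomitant medication, exercise or ambulation".
- **Randomisation, allocation concealment and blinding procedure:** "Participants will be randomised into one of the treatment groups using a computer-generated randomisation table", and "An independent biostatistician will generate the randomisation list which will be provided to the manufacturer". The ratio is 1:1:1:1, so 52/4 = 13 per arm. No stratification factor or block is named, and none is ruled out.
- **Statistical analysis:** mean changes in the clinical scales are assessed by a mixed model for repeated measures "with treatment, week, and treatment-week interaction as fixed effects and intercept as the only random effect; baseline value will be the covariant". A more detailed analysis plan is to follow before database lock.

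The article does not say how many participants each service will enrol, whether the services differ in outcome, or who rates the PANSS.

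**The concern.** The model is a stated choice and not a gap. The article names the fixed effects, says that the intercept is the only random effect, and names the covariate. Health service appears in none of these, although it is known for everyone before randomisation and the design gives some reason for outcomes to vary with it.

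Two situations are possible:

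- **Allocation not stratified by service.** The site mix of two arms of 13 will differ by chance. Any difference between services in six-week change then adds noise to the dose contrasts that the model could have removed.
- **Allocation stratified by service.** The arms are balanced on site, but a model without site leaves the between-service variance in the residual. The standard error is then too large for the design that was used.

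Precision is at stake in either case. Prespecification matters too: the article plans baseline comparisons but names no adjustment beyond the baseline value. Adding site only after an imbalance had been seen would be data-driven.

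**Working it through.** **The plan's own figure.** The plan gives no figure for site. Its only related figure is power of at least 80% for an effect size of 0.55 with 52 participants and 20% attrition. With 52 x 0.8 = 41.6 evaluable, a four-group one-way test with Cohen's f = 0.55 has 81.7% power, so the figure reproduces on that reading. Read as a pairwise standardised difference, 0.55 gives 24.0% at 10.4 per arm. Nothing below depends on which reading was meant.

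**Inputs from the article.** Two services; 13 per arm; PANSS SD 10 to 15; AR(1) correlation 0.815.

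**Inputs assumed.** Split between services 50:50 (70:30 as a check). Difference between services in baseline-adjusted outcome of 0, 0.25, 0.5 or 1.0 residual SD. There is one complete outcome per participant, with residual SD 1.

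**Step 1: chance imbalance if the list is not stratified.** The difference in site share between two arms of n = 13 drawn from N = 52 has variance p(1-p) x N/(N-1) x 2/n.

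- 50:50: 0.25 x 52/51 x 2/13 = 0.0392, SD 0.198.
- 70:30 (36 of 52): 0.213 x 52/51 x 2/13 = 0.0334, SD 0.183.

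Simulation gives SDs of about 0.20 and 0.18. A gap of at least 3 of 13 participants occurs in about 33% of trials (50:50) or 29% (70:30). A gap of at least 4 of 13 occurs in about 17% at 50:50.

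**Step 2: what this does to a dose contrast.** At a 0.5 SD difference, the chance shift has SD 0.198 x 0.5 = about 0.10 SD. The standard error of the contrast is about 0.40 SD, so site carries about (0.10/0.40)^2 = 6% of its variance. In PANSS points, taking the stated SD as the residual SD, the shift is 1 to 1.5 points against a standard error of 4 to 6.

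**Step 3: adding the site term, unstratified list, 50:50.** There were 8,000 simulated trials per scenario. Power is for a pairwise difference of 0.55 SD at an unadjusted two-sided 0.05.

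| Difference between services | SE without site | SE with site | Change | Power without | Power with |
|---|---|---|---|---|---|
| 0 | 0.390 | 0.394 | +1% | 28.2% | 27.8% |
| 0.25 SD | 0.393 | 0.394 | under +1% | 27.2% | 27.1% |
| 0.5 SD | 0.403 | 0.395 | -2% | 26.5% | 27.6% |
| 1.0 SD | 0.438 | 0.395 | -10% | 23.6% | 27.3% |

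Type I error was 4.6% to 5.6% across all scenarios, with or without the term (Monte Carlo standard error about 0.25 points). At 70:30 and 1.0 SD the standard error goes from 0.431 to 0.395, a fall of about 8%.

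**Step 4: if the list is stratified.** Site is then balanced between arms, and the term costs essentially nothing. Leaving it out inflates the residual variance by about 0.25 x d^2, where d is the difference between services in SD. The ratio of standard errors, with site to without, is about 1/sqrt(1 + 0.25d^2):

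- d = 0.5: 1/sqrt(1.0625) = 0.970, or -3%.
- d = 1.0: 1/sqrt(1.25) = 0.894, or -11%.

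**Step 5: what the baseline covariate already removes.** The correlation between baseline and week 6 is 0.815^3 = 0.541 if 0.815 applies per visit, or 0.815^6 = 0.293 if it applies per week. A constant 0.5 SD offset present at baseline then leaves 0.5 x (1 - 0.541) = 0.23 SD or 0.5 x (1 - 0.293) = 0.35 SD. A difference between services in change after baseline is not removed this way.

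**The case against.** The strongest case against raising this is that nothing is misstated. A model without site is valid under randomisation and common in a small two-site phase II trial. The gain is negligible for differences up to 0.5 SD. The larger gain needs a full 1.0 SD difference, which nothing in the article supports. Individualised care implies variation between patients rather than between services, and both services work to the same state standard. The coming analysis plan could still add a covariate. Most of this stands, and it is why the point is minor. It does not remove the point, because the article has already listed the terms and site is not one of them.

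Four stronger readings are tempting, and the document does not support them.

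- A reader might infer that site differences bias the dose effects. Imbalance under randomisation is a chance event that the standard error already carries, and type I error stays near 5%.
- A reader might infer that rater differences between services enter the contrasts. No section links raters to services, and the baseline covariate absorbs part of any stable offset.
- A reader might take the single list as proof of unstratified allocation. A stratified list is still a list, and an article often leaves this to the full protocol.
- A reader might infer that site could reorder the doses. At a 0.5 SD difference, ordinary sampling error is about four times the chance shift from site.

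**Conclusion.** The point holds as a minor one about precision. The listed efficacy terms omit the one design factor that is known for every participant and cannot be affected by treatment. With a 50:50 split, including it costs about 1% of the standard error at worst. It saves 2 to 3% at a 0.5 SD difference between services and 10 to 11% at 1.0 SD. The lower figure in each range is for an unstratified list and the higher for a stratified one. The dose contrasts are not biased either way.

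The split and the difference are assumptions. The calculation uses one complete outcome per participant rather than the full repeated-measures model with dropout. The conversion to PANSS points is rough, because the residual SD after baseline adjustment is below the stated 10 to 15.

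**What to change.** - **Statistical analysis:** add health service (two levels) to the fixed effects of the efficacy model, or state why it is left out. The detailed analysis plan is still to be finalised before database lock, so this remains possible even if recruitment has begun. It should be settled before allocation is revealed.
- **Randomisation:** have the independent biostatistician generate the list in permuted blocks within each health service, if this is not already done, and say in the text which applies. If allocation has already started from an unstratified list, make the model change alone.

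The cost is one sentence in each section, one degree of freedom, and at worst about 1% of the standard error. With blocks within service, arm totals may depart slightly from 13 when the last block at a service is incomplete. A main effect removes the average difference between services after baseline. A difference that builds up over the weeks would be removed only in part.

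### As written, the efficacy model pools one variance and one baseline slope over weeks 2, 4 and 6; under the planning correlation, week-6 type I error is about 7–9%, not 5%

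*Protocol article*

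**What the plan says.** All references are to the protocol article.

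- **Statistical analysis** gives the model for mean changes in clinical assessments: fixed effects for treatment, week and their interaction, with "intercept as the only random effect; baseline value will be the covariant". It calls the method MMRM, states no residual covariance, and defers further detail to an analysis plan to be finalised before database lock. On error control it says that P "values will be based on 2-tailed tests with significance levels of 0.05 corrected for multiple comparisons", without naming the correction.
- **Sample size justification** describes the primary analysis as "comparing total PANSS scores across 4 time points (baseline, 2, 4, and 6 weeks) across 4 dose groups", and plans on this figure from a previous trial: "The autoregressive (AR(1)) correlation between weeks was estimated at 0.815".
- **Clinical outcome measures** fixes the primary comparison: "The mean change in scores from baseline to week 6 (end of the study) will be compared between study arms".

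**The concern.** With a random intercept and nothing else, the model assumes the same variance at every visit, the same correlation between every pair of visits, and one baseline slope throughout. If correlation decays with time, baseline predicts week 2 well and week 6 poorly, so the scatter left after adjusting for baseline grows over follow-up. The model averages that scatter over three visits and applies the average to week 6, where it is too small.

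The week-6 contrast is the primary one. Its p-values and confidence intervals would be too optimistic, and a multiplicity correction cannot repair a standard error that is wrong to begin with. In a dose-finding trial with 13 people per arm, the practical risk is carrying an ineffective dose forward more often than the stated error rate allows.

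A smaller matter is that the sample size text counts baseline among the response times while the analysis text makes it the covariate.

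**Working it through.** **Inputs.** From the article: 52 participants allocated 1:1:1:1, so 13 per arm; visits at weeks 0, 2, 4 and 6; AR(1) correlation 0.815; two-sided 0.05; random intercept, baseline covariate. Assumed here: constant variance σ² at every visit, pure AR(1) decay, complete data, and no residual structure beyond independent errors. The article does not make clear whether 0.815 applies per week or per two-week visit, so both are shown. The type I error does not depend on the SD.

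**The plan's own figures.** The target on this point is 5%. Week-6 ANCOVA, which equals an unstructured model with baseline-by-week when data are complete, gives 4.8–5.1% in simulation, so 5% is attainable. The power statement (80% at effect size 0.55) reproduces if 0.55 is Cohen's f (0.798 with 40 evaluable, 0.821 with 42). The article does not say so, and nothing below depends on it.

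**Step 1. Correlation r of each visit with baseline.**
- Per week: 0.815² = 0.664, 0.815⁴ = 0.441, 0.815⁶ = 0.293.
- Per visit: 0.815, 0.815² = 0.664, 0.815³ = 0.541.

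**Step 2. Variance given baseline, 1 − r², in units of σ².**
- Per week: 0.559, 0.805, 0.914; mean 0.759. SE ratio √(0.759/0.914) = 0.911.
- Per visit: 0.336, 0.559, 0.707; mean 0.534. SE ratio √(0.534/0.707) = 0.869.

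**Step 3. The specified model, with one slope.** The fitted slope b is the mean of the three r values. The variance about it at each visit is 1 − 2br + b², and the model uses the mean of the three.
- Per week: b = 0.466; variances 0.598, 0.806, 0.944; mean 0.783. SE ratio √(0.783/0.944) = 0.911.
- Per visit: b = 0.674; variances 0.356, 0.559, 0.724; mean 0.546. SE ratio √(0.546/0.724) = 0.868.

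The week-6 standard error is therefore 9% or 13% too small.

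**Step 4. Large-sample type I error, 2[1 − Φ(1.96 × SE ratio)].**
- Per week: 1.96 × 0.911 = 1.785, giving 7.4%.
- Per visit: 1.96 × 0.868 = 1.702, giving 8.9%.

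**Step 5. Simulation at the trial's size.** Runs of 10,000 to 20,000 null trials each, 13 per arm, random-intercept REML fit:

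| Test at nominal 5% | 0.815 per week | 0.815 per visit |
|---|---|---|
| One dose vs placebo, week 6 | 7.1–7.7% | 8.5–9.2% |
| Same, 20% dropout, last observation carried forward | 7.4% | 8.3% |
| Any of three doses, Bonferroni (an assumption) | about 7–8% | about 9–10% |
| Effect averaged over weeks | about 5% | about 5% |
| Week 2 | about 2.5% | about 1.6% |

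**Step 6. Would AR(1) residuals repair it?** With baseline as covariate, replacing the random intercept by a constant-variance AR(1) residual, or adding one to it, leaves the large-sample error at 7.5% or 9.0%, because one variance is still pooled over visits. An unstructured covariance returns it to 5.0%.

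**Step 7. Sensitivity to the correlation pattern.** Suppose 50% of the variance is a stable person effect and 15% is visit noise (both assumed), with the lag-1 correlation unchanged. Correlations with baseline become 0.664, 0.577, 0.536 (per week) or 0.815, 0.784, 0.755 (per visit). Step 3 then gives SE ratios of √(0.649/0.716) = 0.952 and √(0.384/0.431) = 0.945, and type I errors of 6.2% and 6.4%.

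**The case against.** The strongest reply is that the article calls the intercept the only random effect, not the only covariance structure. Residual covariance is specified separately in a mixed model and is commonly left to the analysis plan, which is not shown here. A visit-specific or unstructured residual there would remove the problem. This stands as a condition on the figures. It does not dispose of the point: the article fixes the random effect and covariate, and the most obvious addition, a constant-variance AR(1) residual, does not help with baseline as covariate.

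A reader might go further than the document allows in three ways.

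- **That the random intercept contradicts the AR(1) figure.** The two can coexist in one model. If baseline is a response, errors are AR(1) and there is no baseline covariate, simulation puts the change-to-week-6 contrast at 5.4–5.5%. The cause is the pooled variance and single slope more than the shape of the correlation.
- **That this trial's data are known to follow AR(1).** The 0.815 comes from a previous trial, which the Background describes as early psychosis over 12 weeks. This trial enrols people with persistent illness and PANSS total of at least 70. A stable person effect would reduce the inflation.
- **That baseline will be both response and covariate.** Such a model would have a type I error of about 11–14%, but no single section prescribes it. The sample size text lists "comparing total PANSS scores across 4 time points (baseline, 2, 4, and 6 weeks" and the analysis text uses baseline as covariate. That mismatch calls for alignment only.

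**Conclusion.** The concern holds conditionally. If the model is fitted as written with independent equal-variance errors, and the planning correlation applies as constant-variance AR(1), the standard error of the primary week-6 contrast is about 9–13% too small. Its type I error is then about 7–9% rather than 5%, or about 6% if part of the correlation is a stable person effect. The range reflects the two readings of 0.815. Only late-visit contrasts are inflated: the effect averaged over weeks keeps its level and week 2 is conservative. Familywise figures rest on Bonferroni, which the article does not name. It is not established that the trial will be analysed with an inflated error rate, because the analysis plan may supply another covariance. This should be fixed before database lock; it is not a fatal flaw.

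**What to change.** In the analysis plan, and in the protocol text where it can still be amended, specify:

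- response: change in PANSS total at weeks 2, 4 and 6;
- fixed effects: treatment, week, treatment-by-week, baseline and baseline-by-week;
- unstructured within-subject covariance in place of the random intercept (three variances and three covariances, feasible with 52 people), with a pre-stated fallback that keeps visit-specific variances, such as heterogeneous AR(1);
- REML with Kenward-Roger degrees of freedom;
- primary contrasts: each dose versus placebo at week 6.

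In the sample size section, describe baseline as the covariate and weeks 2, 4 and 6 as the response times.

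The change is wording only. Under the planning correlation, week-6 confidence intervals become about 10–15% wider (1/0.911 = 1.10; 1/0.869 = 1.15). The visit-specific baseline slope recovers a little of this: √(0.914/0.783) = 1.08 and √(0.707/0.546) = 1.14. The added width corrects an understated standard error, but with 13 per arm the sponsor should expect some loss of nominal power at week 6.
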